## Abstract

**Background:**

Paralympic sport provides sporting opportunities for athletes with a disability, with the Paralympic Games as the main event. Participation in sport is, however, associated with a significant risk for sustaining injuries and illnesses. Our knowledge of sports-related injuries and illnesses in Paralympic sport is very limited and there are no large-scale epidemiological cohort studies. The purpose here is to present a protocol for a prospective longitudinal study: The Sports-Related Injuries and Illnesses in Paralympic Sport Study (SRIIPSS).

**Methods/design:**

An argument-based method for investigation of design problems was used to structure the study protocol. The primary requirement of the protocol is to allow prospective studies over time and include exposure to both training and competition. To reflect the complexity of Paralympic sport with athletes’ pre-existing impairments, use of assistive equipment, pain and other and medical issues, it is required that the data collection system is specifically adapted to Paralympic sport. To allow the collection of data, at the same time as there is limited access to coaches and medical personnel, it is advantageous that data can be collected online directly from the athletes. Based on this a self-report athlete monitoring system will be developed, where the athletes can enter data weekly via their mobile phones or lap-tops. Data will be collected from around 100 Swedish Paralympic athletes for approximately 1 year, which will allow us to i) prospectively estimate the annual incidence of sports-related injuries and illnesses and ii) explore risk factors and mechanisms for sustaining sports-related injuries and illnesses based on athlete exposure and training loads.

**Discussion:**

For effective implementation of injury and illness prevention measures, comprehensive epidemiological knowledge is required. This study will be the first prospective longitudinal self-report study of sports-related injuries and illnesses in Paralympic sport over a longer period of time. The results will eventually contribute to the development of evidence-based preventive measures specifically adapted to Paralympic sport in order to provide safe and healthy sport participation. Thereby, the project will be of relevance for Paralympic athletes at all levels and to the Paralympic Movement.

**Trial registration:**

The study is registered at ClinicalTrials.gov (Identifier: NCT02788500; Registration date: 22 May 2016).

## Background

Sport for athletes with disabilities has existed for more than 100 years. Today, the global network ‘The Paralympic Movement’ provides sporting opportunities for Paralympic athletes with physical, visual or intellectual impairments, from grassroots to elite level, with the Paralympic Games as the main event. During the past decades, Paralympic sport has seen a large development in both the number of athletes, sports performance and technology [1], and many Paralympic athletes have reached performances similar to able-bodied elite athletes [2].

It is well-known that physical activity and participation in sport generates several positive health effects [3, 4]. Low physical fitness and reduced physical activity is associated with many adverse health events, including major non-communicable diseases [5]. Participation in sport is therefore of great importance, especially for persons with disabilities, as individuals with a chronic disease or disability have lower physical fitness compared to non-disabled individuals [6]. Sport is today included in most rehabilitation programs for people with disabilities, to promote both physical and psychological well-being [7, 8].

### Injuries and illnesses in Paralympic sport

Participation in sport is, however, associated with a significant risk for sustaining injuries and illnesses that may have long-lasting effects, including mortality, morbidity and high costs for society [9, 10]. Remaining free of injury and illness has therefore become a fundamental component of successful performance in sport [11].

Previous research has shown that injury rates in Paralympic sport are generally high with a trend towards more injuries compared with sport for able-bodied athletes [12]. Injury patterns related to the impairment, the equipment involved and the specific mechanics of the sport have been proposed to be related to the injuries [13]. Maintaining health in athletes with already existing disabilities can be problematic. The athletes may have complex pre-existing medical conditions, such as neurodegenerative disorders, spinal cord injury, amputations, rare syndromes with anomalies in different body systems, vision loss and intellectual impairments, and medical issues like autonomic dysreflexia, infections, hyperthermia, skin lesions, spasticity, fatigue, pain and epilepsy can be present [13]. Moreover, the athletes may be exposed to repetitive and sometimes improper biomechanical load in their daily life [14, 15]. Based on the facts that the Paralympic Games is now one of the world’s largest multi-sport events [1] and that training intensity and performance levels have increased during the past years [16], there are surprisingly few epidemiological studies covering sports-related injuries and illnesses in Paralympic sport. Thus, further studies are needed to ensure the development of safe participation in Paralympic sport.

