**Fig. 1 Fig1:**
[figure not shown]
Requirements and associations underlying the study protocol for The Sports-Related Injuries and Illnesses in Paralympic Sport Study (SRIIPSS)

The primary requirement of a protocol for longitudinal epidemiological studies in Paralympic sport is to allow prospective studies that cover at least an entire season and include exposure to both training and competition. Second, to reflect the complexity of Paralympic sport, for example pre-existing impairments, use of assistive equipment, pain and other and medical issues, it is required that the design of a surveillance system is specifically adapted to Paralympic sport. Third, to allow the collection of epidemiological data and individual training behaviors, at the same time as there is limited access to coaches and medical personnel, it is advantageous that longitudinal data can be collected online directly from the athletes. There is also increasing evidence that psychological and behavioral factors contribute to the process leading to several sports injuries [50, 51]. Therefore, a psychological profile will be added to identify factors and behaviors related to pain and other activity-limiting sensations [50].

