Baseline data	Gender, age, impairment, sport, training hours, previous injury/illness, medication, aids, anthropometrics, pain	SRIIPSS protocol for baseline data
Psychological profile	Perceived motivational climate	Perceived Motivational Climate in Sport Questionnaire (PMCSQ)
	Active coping	BRIEF COPE
	Body consciousness and body competence	Body Consciousness Questionnaire Scale (BCQ-s)
	Hyperactivity	Diagnostic and Statistical Manual of Mental Disorders (DSM-IV)
	Psychological commitment to exercise	Commitment to Exercise Scale (CTeS)
	General well-being	Likert-scale
Weekly athlete report	Injuries, illnesses, pain, psychological stressors, amount of training and competition, training intensity, sleep	SRIIPSS protocol for weekly athlete data Likert-scale
Injury report	Onset of injury, mechanism of injury, present symptoms, type of injury, impairment-related factors, medical contacts	SRIIPSS protocol for weekly injury data
Illness report	Onset of illness, present symptoms, type of illness, impairment-related factors, medical contacts	SRIIPSS protocol for weekly illness data
Injury/illness closure form	Diagnosis of injury/illness, severity of injury, treatment, perceived risk factors	SRIIPSS protocol for injury/illness closure data

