### Outcome measures

#### Baseline data

Baseline data will be collected using a web-based questionnaire including: i) participant characteristics (i.e., gender, age, height and weight); ii) demographic data; iii) impairment characteristics (i.e., type of impairment, use of assistant devises, medications); and iv) sport characteristics (i.e., type of sport, preconditions, hours per week involved in training and competition). The athletes will also be asked about existing injuries, illnesses and pain. In addition, women will be asked about menstruation and use of contraceptives.

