### Athlete weekly e-diary

To collect data on new sports-related injuries and illnesses as well as on exposure, the athletes will be asked to fill in a weekly e-dairy based on one developed by Jacobsson et al. [33] and adapted for Paralympic sport. Each week, an alert is automatically sent to the participants’ email address and mobile phone, asking them to fill in the weekly questionnaire about their current health status (injuries, illnesses and pain), the amount of training, intensity of training, whether the training is performed at full capacity, competitions, sleep, general well-being and medical contacts. In addition, anxiety/depression and pain/discomfort will be evaluated using two questions from EQ-5D [61].

If the athlete reports a new injury or illness in their weekly e-dairy, a link to an injury or illness report form will be provided, where additional information on the incident are to be reported. The study coordinator (KF) monitors the reported data. If a participant is absent from training because of an undiagnosed injury or illness lasting longer than 3 weeks, the participant will be contacted by phone or email. The athletes will be asked to go through an examination by a sports physician or sports physiotherapist to confirm the clinical diagnosis, in order to validate the data.

Internal training loads will be recorded based on a modified version from Gabbett & Jenkins [62] and Foster et al. [63]. The athletes will be asked to estimate their total rating of perceived exertion (RPE) during the past week on a 0–10 point RPE-scale [62]. Previous research has demonstrated that the RPE method is a valid method to quantify exercise training during a wide variety of exercise types [63], and the method has also been shown to provide valid estimates when compared to heart rate and blood lactate concentration. The training load will be calculated by multiplying the training session intensity with the duration of the training during the week and will be further analysed with the relationship of injury/illness, acute loads and chronic loads [43, 62, 64].

Assistance will be provided, if necessary, for athletes with vision or intellectual impairment, or severe physical impairment. At the start of the study the athletes will be educated about the importance of monitoring. Feedback will be given, if desired, to allow data to be used to the athletes’ benefit.

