### Injury report form

The injury report form is a modified version of the form described by Jacobsson et al. [33], originally based on the soccer consensus by Fuller et al [27] and the International Olympic Committee (IOC) groups [30]. This injury report system has been shown to be feasible for self-report data in other individual sports, such as athletics [31]. The athletes will be asked about the onset of injury, mechanism of injury, contributing factors, anatomical site and recurrence of earlier injury. The athletes will also be asked about presenting symptom(s) or sign(s) and suspected aetiology (a list of common categories of causes is provided). The system is further adapted to be applicable to athletes with impairments. For example, questions will be added regarding the impairment and equipment used.

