### Statistical analysis plan

The primary variables for the descriptive analyses are records of the incidence of sports-related injuries and illnesses, i.e., recordings of injury or illness events that are conditioned on that the participant is ‘healthy’ at the start of data collection period. Incidences will be calculated separately for injuries and illnesses. The incidence rates will be calculated as the number of new incidents divided by total athlete exposure hours (per 1000 h of sport participation). Health-incidents not related to sport will be analyzed separately. All events will be evaluated according to the mechanism of sports-related injuries and illnesses (independent variables). The data will be assessed for normality and will be presented using quantitative descriptive statistics (mean, median, standard deviation, minimum and maximum for continuous data and frequency and proportion (%) for categorical data). Differences in proportions between different categories (e.g., age-groups, gender, impairments, previous injury, competition frequency and level of severity of impairment) will be analyzed as covariates using chi-square statistics. The primary end point for the injury risk analyses will be time to injury. The incidence data will be further analyzed with the Kaplan-Meier survival analysis method, the log-rank test and Cox proportional hazards regression. To analyze the relationship between training loads and injury and illness incidence, Pearson product moment correlation coefficients will be used. A significance level of 0.05 and 95 % confidence intervals will be used in all tests. The data will be analyzed using IBM SPSS Statistics version 23.

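### The only method named for training load versus injury and illness is an unadjusted Pearson correlation, although impairment and assistive-device use are recorded and could be adjusted for

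*Protocol article*

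**What the plan says.** All references are to the protocol article.

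- **Background, Injuries and illnesses in Paralympic sport.** Impairment, equipment and the mechanics of the sport are reported as proposed correlates of injury. The section adds that "the athletes may be exposed to repetitive and sometimes improper biomechanical load in their daily life".
- **Purpose.** Aim ii is to explore risk factors and mechanisms using athlete exposure and training loads.
- **Study design and rationale.** The data collection system must reflect "pre-existing impairments, use of assistive equipment, pain and other and medical issues".
- **Table 2 and Baseline data.** Baseline items include impairment, sport and "previous injury/illness, medication, aids, anthropometrics, pain". The baseline section lists "impairment characteristics (i.e., type of impairment, use of assistant devises, medications"). On the injury form, "questions will be added regarding the impairment and equipment used".
- **Athlete weekly e-diary.** "The training load will be calculated by multiplying the training session intensity with the duration of the training during the week". The measure therefore counts sport only.
- **Statistical analysis plan.** Incidence is the "number of new incidents divided by total athlete exposure hours (per 1000 h of sport participation"), again sport only. For load, "To analyze the relationship between training loads and injury and illness incidence, Pearson product moment correlation coefficients will be used". An open list of factors, including impairments and severity of impairment, is attached to chi-square tests of proportions. Cox regression is planned for the incidence data, with time to injury as the end point. Its covariates are not listed, and it is not named for load.

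**The concern.** A Pearson coefficient relates two variables and has no place for a third. The cohort is very mixed: Table 1 lists ten impairment types and 28 sports (22 summer, 6 winter). The article itself names impairment and equipment as possible determinants of injury and collects both, then fixes a load analysis that can use neither.

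If athletes who use devices, or who have certain impairments, train a different amount and also have a different injury rate, the pooled correlation mixes that group difference with the effect of load. Aim ii is meant to inform prevention. A load association weakened, strengthened or created in this way would be a poor basis for it.

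**Working it through.** **1. Nothing to reproduce.** The article uses a total population design and states no power, event or effect figure. It gives no share of device users and no difference in load or injury rate between groups. Everything below except the number of athletes (about 100, Setting and participants) and the 0.05 level (Statistical analysis plan) is assumed. The level is taken as two-sided.

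**2. When does pooling create a correlation?** Take two groups with no load-injury association inside either. Let p be the share of device users, and dX and dY the group differences in load and injury rate in within-group SDs. Then

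r = p(1−p)·dX·dY / √[(1 + p(1−p)dX²)(1 + p(1−p)dY²)].

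The rejection probability uses Fisher's z with N = 100. The critical |r| is tanh(1.96/√97) = 0.196.

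| p | dX | dY | crude r | chance of p < 0.05 |
|---|---|---|---|---|
| 0.3 or 0.5 | 0 | any | 0 | 5% |
| 0.3 or 0.5 | any | 0 | 0 | 5% |
| 0.3 | −0.5 | 0.5 | −0.05 | 8% |
| 0.5 | −0.5 | 1.0 | −0.11 | 19% |
| 0.3 | 1.0 | 1.0 | 0.17 | 41% |
| 0.5 | 1.0 | 1.0 | 0.20 | 51–52% |

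So a difference in only one of the two does no harm. A difference in both can give either sign.

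**3. What could happen to a real effect?** Assume 40% device users, a within-group SD of log load of 0.5, a base rate of 2 injuries a year and a true rate ratio of 1.30 per doubling of load. Let d be the log ratio of mean load in users, and g their log rate ratio for injury. The shift in the crude log rate ratio per doubling is approximately

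ln 2 × 0.24·d·g / (0.25 + 0.24·d²), with 0.24 = 0.4 × 0.6.

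- Rate 1.25 times, load 10% less: d = −0.105, g = 0.223, shift −0.015, crude 1.30·e^(−0.015) = 1.28.
- Rate 1.5 times, load 20% less: d = −0.223, g = 0.405, shift −0.057, crude 1.23.
- Rate 2 times, load 30% less: d = −0.357, g = 0.693, shift −0.147, crude 1.12.

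A Poisson simulation with 400,000 athletes gives the same crude values. Adjusting for device use returns 1.30 each time, as it must, because device use is the only confounder built in. In the third case Pearson r is 0.12 pooled, against 0.26 (non-users) and about 0.34 (users) within groups. With N = 100, r = 0.12 gives z = atanh(0.12)·√97 = 1.19, so power is about 22%.

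**4. Size against sampling error.** With about 225 events, the standard error of the log rate ratio per doubling is roughly 0.693/(0.5·√225) = 0.092. The three shifts are then 0.2, 0.6 and 1.6 standard errors. Only the most extreme scenario is large beside chance.

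**The case against.** The strongest case against has four parts.

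- **Covariates may sit in a fuller plan.** The factor list is open and already includes impairment and its severity, the Injury closure form section promises analysis by classification and impairment type, and the Cox covariates may be set elsewhere. This is fair for the Cox model. It does not rescue the load analysis, because extending a list of chi-square factors cannot adjust a Pearson coefficient, and the coefficient is a stated choice.
- **Load may be compared within athletes.** The e-diary section says load will also be examined through acute and chronic loads. If each athlete is compared with their own chronic load, a fixed trait such as device use largely drops out. This stands in part. The section names no method, and the unit of the Pearson analysis (athlete or athlete-week) is not stated.
- **Injuries must result from sport.** The injury definition excludes injuries due to daily-life load alone. This narrows the route for bias, though mixed causation remains possible.
- **Nothing singles out devices.** Sport and impairment are equally plausible confounders. This stands, and it is why the point covers impairment as well as device use.

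A reader might infer more than the documents support. They do not make daily-life load part of the study's exposure: the remark is background, worded as a possibility, and the sport-only measure matches aim ii. They do not show that the load effect is confounded, since nothing links device use to training load. Nor do the scenarios make low load look harmful: the crude ratio stays above 1 in all three.

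**Conclusion.** The point holds in limited form. The only method named for training load versus injury and illness cannot account for impairment or device use, although the article treats both as possible determinants of injury and records both. The crude association may therefore be confounded.

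Whether it is, in which direction and by how much cannot be read from the documents. Under the assumptions above, the effect ranges from none (groups differ on only one of load and injury rate) to a rate ratio of 1.30 seen as 1.12, or a false-positive rate near 52%. These figures show what is possible and are not estimates for this cohort. It is a minor but worthwhile improvement to the analysis.

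**What to change.** Replace or supplement the Pearson correlation with a load-injury regression, for example a count model or the planned Cox model with load as a covariate. Adjust for, or stratify by:

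- recorded device use, as user versus non-user or as the baseline form codes it;
- a collapsed impairment grouping, for example the physical, visual and intellectual groups that the article already uses.

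Report this for all injuries and for gradual-onset injuries. State that device use is only a proxy and that unmeasured daily-life load remains a limitation. The article does not say whether the form separates daily-life from sport devices, so finer device categories should not be promised without checking it.

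The cost is analysis wording, with no new data for the user/non-user version. One degree of freedom for device use and two for three impairment groups make three in about 100 athletes, with slightly wider intervals.

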### Sports injury research

Recent research has shown that several categories of sports-related injuries are preventable [17–19]. However, for effective implementation of injury prevention measures, comprehensive epidemiological knowledge is required [9, 20]. To reduce overtraining, injuries and illnesses, regular monitoring of athletes is an important aspect in athletic preparation [21, 22]. Although the International Paralympic Committee (IPC) has successfully implemented an epidemiological surveillance system during the Paralympic Games [23], there is still a lack of longitudinal prospective data following Paralympic athletes over entire training seasons [12]. A recent review identified large differences in injuries across sports and highlighted the need for sport-specific studies [24]. Current studies within Paralympic sport vary in quality and have mainly recorded injuries related to trauma, medical attention or time loss. Most studies are retrospective and have only recorded injuries during competitions. In addition, a diversity of injury definitions have been used and most studies have not examined impairment-related risk factors and injury severity [12, 25]. Thus, there is a need for further longitudinal epidemiological studies that prospectively assess sports-related injuries and illnesses in Paralympic sport based on risk exposure.

Today, most injury surveillance systems exist in professional and commercial able-bodied elite sport settings [26], for example soccer, tennis and rugby [27–29]. In addition, many of the surveillance systems require that medical practitioners complete the injury report form [23, 28–30]. However, the characteristics, preconditions and contexts differ between sports [31, 32]. For example, medical attention injuries may be difficult to apply when there is limited access to medical personnel [33]. It has also been proposed that some methods for injury registration may underestimate overuse injuries [34]. Also, in terms of injury capture rates, medical staff may underestimate the injury burden compared to athletes themselves [32].

